## Abstract

**Background::**

Femoral intertrochanteric fractures (ITF) occur frequently in the elderly, accounting for 45% of all hip fractures. Postoperative anemia after fracture tends to cause ischemia, hypoxia in cells, tissues and organs, increasing the rate of blood transfusion, risk of infection, disability and mortality. Meanwhile, traditional Chinese medicine is widely used in the treatment of anemia for activating blood circulation and removing blood stasis.

**Methods::**

This study is a prospective, outcome assessor-, and data analyst-blinded randomized controlled clinical trial. The objective of this proposed study was to investigate whether Shengyu Decoction could improve the symptoms of anemia after proximal femoral nail antirotation in elderly ITF patients. After qualifying for screening, patients will be randomized into 2 groups with an allocation ratio of 1:1. Hemoglobin concentration, HBL, and HHS score are outcome measurements. The other outcomes also included time to get out of bed, discharge to home, 30-day readmission rates, and mortality.

**Discussion::**

ITF is commonly occurring in senior citizens, and those who are senior in age generally suffer 1 or more basic diseases, whose nutritional status is already poor. Trauma and surgical stimulation not only aggravate the existing disease or induce corresponding cardiovascular complications, but also worsen the nutritional status, which can easily cause postoperative anemia in patients. Because of the limited clinical modalities available for the treatment of postoperative anemia after fracture surgery, and most of them have various side effects that are not easily tolerated by the elderly. Therefore, from a traditional Chinese medicine perspective, we proposed a protocol using mild Chinese herbal decoction to treat postoperative anemia in ITF.

Registration number: OSF Registration number: DOI 10.17605/OSF.IO/JQ6ZF.

## Introduction

1

Femoral intertrochanteric fractures (ITF) occur frequently in the elderly, accounting for 45% of all hip fractures. With the acceleration of the aging population, the incidence of femoral intertrochanteric fractures is also increasing.^[1,2]^ At the same time, complications caused by long-term bed rest in nonsurgical patients often lead to high disability and high mortality. Survivors are prone to various sequelae, making this disease an important public health problem. In addition, the high cost of treatment makes it difficult. Both national health and social economy have a serious impact.^[3]^

Surgery is currently recognized as the main treatment method, which can reduce pain, promote joint functional recovery, avoid many complications caused by long-term bed rest, and improve the quality of life of patients.^[4]^ Among them, the proximal femoral nail antirotation (PFNA) has the advantages of easy operation, less trauma, and stable fixation. Its characteristic is that it maintains the firm fixation and biomechanical stability of AO. The essence of BO and minimally invasive surgery is suitable for various types of femoral intertrochanteric fractures, and is currently one of the main clinical surgical methods.^[5,6]^ However, with the popularization and application of PFNA in the treatment of ITF, more and more scholars have found that although the amount of bleeding during the operation of PFNA is small, some patients show different degrees of anemia after the operation. Li analyzed the perioperative blood loss in 123 patients with ITF who underwent PFNA and found that the total blood loss from the admission day to the first and third postoperative day was 693.5 ± 359.6 mL and 863.8 ± 429.9 mL, of which the corresponding hidden blood loss was 86.8% and 89.4%, respectively.^[7]^ Tian found that 26 of 79 patients who underwent PFNA received 400 mL of blood transfusion and 22 patients received 800 mL of blood transfusion, warning the orthopedic staff to pay attention to perioperative anemia in PFNA patients.^[8]^ Postoperative anemia after fracture tends to cause ischemia and hypoxia in cells, tissues and organs, increasing the rate of blood transfusion, risk of infection, disability and mortality, triggering blood-borne diseases and affecting immune function, delaying postoperative recovery and prolonging hospitalization.^[9,10]^ Blood transfusion is the most effective way of treating anemia, which enhances hemoglobin concentration and improves anemia in a short term, but there are various severe risks such as viral infections, immune allergic reactions, acute hemolytic reactions, etc. Meanwhile, the current clinical blood use guidelines are all restrictive transfusion thresholds (hemoglobin concentration <8 g/dL).^[11]^ Other treatments include nutritional support, iron supplementation, erythropoietin, erythropoietin, and use of hemostatic drugs, and these modalities are prone to various side effects.

Meanwhile, traditional Chinese medicine (TCM) is widely used in the treatment of anemia for activating blood circulation and removing blood stasis. It functions in many ways, such as engaging in multi-linked and multi-targeted regulation, improving the bone marrow hematopoietic microenvironment, restoring bone marrow hematopoietic function, and improving the quality of life of patients. Therefore, this study followed the principles of prospective, randomized, and controlled, aiming to explore the clinical efficacy of TCM methods on postoperative anemia in ITF patients who underwent PFNA, for the purpose of obtaining more completed information on safety and efficacy, and providing research methods and ideas for the treatment of postoperative anemia in ITF.

## Methods

2

### Study registry

2.1

This research protocol follows the latest consolidated standards of reporting trials 2017 (See Fig. 1 for the flow chart), and Standard Protocol Items: Recommendations for Interventional Trials 2013 statement (see SPIRIT checklist, Supplemental Digital Content Table S1).

**Figure 1 F1:**
[figure not shown]
Study Flow.

### Study design

2.2

This study is a prospective, outcome assessor-, and data analyst-blinded randomized controlled clinical trial. The objective of this proposed study was to investigate whether Shengyu Decoction could improve the symptoms of anemia after PFNA in elderly ITF patients. Elderly patients with an emergency diagnosis of ITF at our institution from January 2022 to December 2023 were enrolled. All patients were treated with PFNA intramedullary fixation at our hospital.

The principal investigator (PI) is responsible for the overall project and organizing Steering Committee meetings. PIs of sub-center departments are responsible for gathering experts to carry out the project. An independent Steering Committee will be responsible for affairs such as participants’ safety, meetings, recruitment and follow-up of participants, and quality control. The coordinating center is responsible for communicating protocol modifications and providing materials. It consists of a 2-week treatment period and a 6-month follow-up period. Outcome assessment at baseline, post-operative days 1, 3, 7, 14 days, 1 month, 3 months, and 6 months postoperatively. (Fig. 1)

### Eligibility criteria

2.3

The inclusion criteria are as follows:

1.Patients aged 60 to 85 years.2.X-ray or CT indicates ITF.3.Treated with PFNA intramedullary fixation.4.First day postoperative test results: hemoglobin concentration <8 g/dL.5.Being willing to give informed consent.^[12]^

The exclusion criteria are as follows:

1.Anemia caused by other diseases.2.Patients are with open fractures or pathological fracture caused by infection, tumor, or tuberculosis.3.Patients are with congenital hip dysplasia or osteonecrosis of the femoral head.4.Failure to understand or sign informed consent.

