### Patient population and recruitment procedure

2.6

Participants will be recruited from Longhua Hospital affiliated to Shanghai University of Traditional Chinese Medicine. Those patients eligible for enrollment and willing to participate in the study were initially evaluated at baseline and then finally identified through a combination of clinical presentation, physical examination, imaging and laboratory tests. Considering the age of the patients enrolled in this study, the investigator must obtain the consent of the patient's immediate family besides the patient's own informed consent to start the trial. Participants will be informed about the required cooperation in the study, the potential benefits of participating in the study, the possible adverse effects, risks and discomforts of participating in the study, and the associated reimbursement costs and confidentiality of personal information. Participants will also be informed of withdrawal from this study at any time during the study and that the investigator may discontinue your participation in this study at any time out of concern for your best interests. A data collection form including all variables of interest and all potential risks will be completed by the corresponding research center. All information obtained will be kept in an e-database for future statistical analysis. Recruitment will start in January 2022 and is expected to end in December 2023. Final follow-up of all participants will be completed on December 31, 2024.

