#### Secondary outcome measurements

2.9.2

HBL: HBL comprises a relatively high percentage of the total perioperative blood loss in ITF patients, which is the dominant cause of postoperative blood loss in intramedullary fixation systems and is strongly associated with postoperative anemia. HBL was calculated based on changes in Hct levels and estimated patient's blood volume (PBV). Following Nadler's formula, PBV (L) = k1∗height (m)^3^ + k2 ∗weight (kg) + k3. For men, k1 = 0.3669, k2 = 0.03219, and k3 = 0.6041, and for women, k1 = 0.3561, k2 = 0.03308, and k3 = 0.1833. In addition, the total red blood cell loss (TRBCL) was calculated according to the Gross formula: TRBCL (L) = PBV∗ (Hctpre − operation − Hctpost − operation), TBL(L) = TRBCL/Hctpre-operation + BVtrans. Finally, it can be derived that HBL(L) = TBL − VBL.^[13–15]^

HHS score: Anemia also interferes with postoperative joint function recovery in hip fracture patients and slows down the overall postoperative rehabilitation progress of patients16.Therefore, the Harris score was used to measure the degree of recovery of the patient's joint function after surgery, indirectly reflecting the patient's anemia. The Harris score consists of 10 questions, with 2 questions in the physician physical examination section (ROM and absence of deformity) and 8 questions in the patient-reported outcomes section.

The other outcomes also included time to get out of bed, discharge to home, 30-day readmission rates, and mortality.

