## Discussion

3

ITF is commonly occurring in senior citizens, and those who are senior in age generally suffer 1 or more basic diseases, whose nutritional status is already poor. Trauma and surgical stimulation not only aggravate the existing disease or induce corresponding cardiovascular complications, but also worsen the nutritional status, which can easily cause postoperative anemia in patients. Because of the limited clinical modalities available for the treatment of postoperative anemia after fracture surgery, and most of them have various side effects that are not easily tolerated by the elderly. Therefore, from a TCM perspective, we proposed a protocol using mild Chinese herbal decoction to treat postoperative anemia in ITF.

Considering this objective, we conducted a systematic literature search before starting this trial to ensure its comprehensiveness. We have thoroughly searched PubMed, MEDLINE, EMBASE, Cochrane Library, ISI web of knowledge, Wan Fang Data, CNKI databases, Vip Journal Integration Platform (VJIP), and Chinese BioMedical databases from the inception to June 2021.

This trial aims to observe the effectiveness and feasibility of this treatment and explore a way to rapidly correct postoperative anemia in TCM and promote patient recovery. Hopefully, this study will provide a theoretical basis and clinical evidence for the treatment of postoperative anemia after PFNA in elderly ITF patients and explore new ideas and methods for clinical treatment.

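### Entry on day-1 hemoglobin alone may mix patients already low on admission with heavy perioperative bleeders; the primary ANCOVA should adjust for preoperative as well as day-1 hemoglobin

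*Protocol article*

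**What the plan says.** The Study design section asks whether the decoction "could improve the symptoms of anemia after PFNA in elderly ITF patients". Under Eligibility criteria (2.3), the only hemoglobin rule for entry is "First day postoperative test results: hemoglobin concentration <8 g/dL". The first exclusion is "Anemia caused by other diseases". No criterion uses hemoglobin before surgery or a required perioperative fall. Section 2.6 says eligible patients are "finally identified through a combination of clinical presentation, physical examination, imaging and laboratory tests".

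The Introduction cites a series of 123 PFNA patients in whom "total blood loss from the admission day to the first and third postoperative day was 693.5 ± 359.6 mL and 863.8 ± 429.9 mL". Section 2.9.2 gives the Nadler and Gross formulas for hidden blood loss, which need a preoperative hematocrit.

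Statistical analyses (2.12) specifies an ANCOVA on the change from before to after treatment, with group as fixed factor and baseline score and research institution as covariates. It does not say whether baseline hemoglobin is the preoperative or the day-1 value.

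**The concern.** A day-1 value below 8 g/dL can be reached in two ways: an ordinary loss from a low admission hemoglobin, or a large loss from a normal one. Nothing in the entry rule separates these routes. If later hemoglobin depends partly on where the patient stood before surgery, two patients with the same day-1 value will have different expected outcomes, and a model holding only the day-1 value leaves that difference in the error term.

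What is at stake is precision, adjustment for chance imbalance in a trial of 36 per arm, and a clear description of whom the result applies to. The validity of the randomised comparison is not in question.

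**Working it through.** **Inputs from the article.** Loss from admission to day 1: mean 693.5 mL, SD 359.6 mL (Introduction). Nadler coefficients for women: 0.3561, 0.03308, 0.1833. Total loss without transfusion = PBV × (Hct pre − Hct post) / Hct pre (2.9.2). Patients per arm: 36 (2.11).

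**Assumptions.** Hemoglobin proportional to hematocrit; loss normally distributed and independent of admission hemoglobin; no transfusion before the day-1 test; body sizes and admission-hemoglobin distributions as stated below. Exclusion 1 is not modelled.

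**Step 1: who meets the entry rule.** For a 1.60 m, 60 kg woman, PBV = 0.3561 × 1.60³ + 0.03308 × 60 + 0.1833 = 1.459 + 1.985 + 0.183 = 3.627 L. The loss needed to reach 8 g/dL is PBV × (1 − 8 / admission Hb).

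| Admission Hb (g/dL) | Loss needed (mL) | Chance of day-1 Hb < 8 |
|---|---|---|
| 13 | 1395 | 2.6% |
| 12 | 1209 | 7.6% |
| 11 | 989 | 20.6% |
| 10 | 725 | 46.5% |
| 9 | 403 | 79.0% |

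At the mean loss the fall is 693.5 / 3627 = 19%, so the patient qualifies only if admission hemoglobin was below 8 / (1 − 0.191) = 9.9 g/dL. For assumed body sizes from a 1.55 m, 50 kg woman (PBV 3.16 L) to a 1.70 m, 70 kg man (4.66 L), this limit runs from 10.3 down to 9.4 g/dL.

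**Step 2: the mix among eligible patients.** Simulation with PBV 3.7 L, admission SD 1.5 g/dL and assumed admission means of 11.0 to 12.5 g/dL:

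- Admitted below 10 g/dL: about 61% of eligible patients at mean 11.0, 51% at 11.5 and 31% at 12.5. At mean 11.5 they are 16% of all patients.
- At or above 8 g/dL on admission: 92% to 99% of eligible patients.
- Mean fall among eligible patients: 2.6 to 3.3 g/dL. At mean 11.5 their mean loss is about 1,020 mL, against 693.5 mL in the cited series.

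Both routes are therefore represented. Over a wider grid (mean 10.5 to 13, SD 1 to 2, PBV 3.0 to 4.65 L), the eligible share admitted below 11 g/dL runs from 8% to 98%, so no single share can be defended.

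**Step 3: what the day-1 value carries.** Among eligible patients in the step 2 scenarios, admission and day-1 hemoglobin correlate 0.50 (mean 11.0) to 0.35 (mean 12.5). Squared, day-1 hemoglobin explains roughly a quarter to an eighth of the variation in admission hemoglobin. The residual SD of admission hemoglobin given day-1 is 1.03 to 1.16 g/dL.

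**Step 4: what the covariate could gain.** For illustration, let day-14 Hb = day-1 Hb + r × fall + error, with error SD 1 g/dL (assumed). Given day-1 hemoglobin, the variance removed by adding preoperative hemoglobin is r² × (residual SD)².

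- r = 0.2: 0.04 × 1.03² = 0.042; share 0.042 / 1.042 = 4%.
- r = 0.6: 0.36 × 1.16² = 0.48; share 0.48 / 1.48, about 33%.
- r = 0: no gain.

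**Step 5: chance imbalance.** At 36 per arm, the standard error of the between-arm difference in admission hemoglobin, given day-1, is 1.03 to 1.16 × √(2/36) = 0.24 to 0.27 g/dL. Multiplied by r = 0.2 to 0.6, this moves the outcome difference by 0.05 to 0.16 g/dL per standard error. It is the loss of step 4 seen another way, not an additional one.

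**The case against.** **Allocation is randomised and the analysis is baseline-adjusted.** Mixed causes therefore cannot bias the comparison. This stands in full; only precision, chance imbalance and interpretation remain.

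**Baseline may not be the day-1 value.** Section 2.2 lists baseline separately from postoperative day 1, so it could be preoperative. This stands as an ambiguity. Two things favour day 1: patients qualify only on the day-1 result, with baseline testing before the envelope is opened (2.5), and 2.12 speaks of change from before treatment. If baseline is preoperative, the day-1 value is the one missing from the model, and naming both still settles it.

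**Covariate lists belong to the analysis plan, and 2.12 promises one.** This is fair for details left open. Here the article states the model and its covariates, so the point improves a stated model and does not complain of an omission. How exclusion 1 is verified may well be left to the full protocol, and it is not pressed.

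**No effect on power is documented.** This also stands: step 4 rests on an assumed recovery fraction and error SD.

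Three stronger readings are tempting and are not supported:

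- A reader might infer that the trial largely enrols anemia that predates surgery. The article gives no admission hemoglobin, and in the step 2 scenarios at least 92% of eligible patients cross 8 g/dL after admission. A low admission value may also reflect bleeding from the fracture itself.
- A reader might infer that exclusion 1 cannot be checked by day 1. History, laboratory tests and a preoperative blood count are available by then.
- A reader might see a contradiction between exclusion 1 and the Discussion, which says "those who are senior in age generally suffer 1 or more basic diseases, whose nutritional status is already poor". That passage can be read as describing susceptibility; the exclusion concerns anemia caused by another disease, not comorbidity as such.

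**Conclusion.** The point holds in a limited form. Entry on day-1 hemoglobin alone can mix patients who were low on admission with heavy perioperative bleeders, and the article's own loss figures make such mixing plausible. The share is unknown. A day-1 baseline truncated below 8 g/dL captures only part of the difference (correlation about 0.35 to 0.50 under the stated assumptions).

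The consequence is lost precision and unadjusted chance imbalance, not bias. Adding preoperative hemoglobin would remove about 4% to 33% of residual variance if later hemoglobin recovers 20% to 60% of the fall with error SD 1 g/dL, and none if recovery is unrelated to the fall. These figures rest on assumed body size, admission-hemoglobin distribution, recovery and error. They show a plausible range and do not estimate this trial's gain.

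**What to change.** In section 2.12, state that the primary hemoglobin ANCOVA includes two prespecified covariates: the day-1 pre-treatment hemoglobin and the preoperative (admission) hemoglobin. This also settles which measurement is meant by baseline. Report both by arm in the baseline table, so that readers can see the mix enrolled.

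No new test should be needed, because hidden blood loss already requires a preoperative hematocrit and the same blood count supplies hemoglobin. The cost is one residual degree of freedom: with 72 patients and an intercept, group and one baseline, 72 − 3 = 69 becomes 68. Entry criteria need not change and recruitment is unaffected. An admission-hemoglobin cut-off is not recommended here: it would slow recruitment, and it could remove patients whose low admission value comes from the fracture.

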### Intervention

2.4

Basic treatments: All patients in both groups were treated with preoperative rehydration, analgesia and anticoagulation, and the relevant departments were consulted to exclude preoperative contraindications; all patients were treated with PFNA intramedullary fixation; postoperative treatments such as rehydration, anticoagulation, analgesia, infection prevention and regular drug changes were given accordingly.

Treatment group: Patients in the trial group were treated with Shengyu decoction granules under basic treatment with 1 dose daily in 2 times for 14 days.

Control group: The control group was treated with placebo on the base treatment, and the placebo was simulated by Shengyu decoction granules, which were required to be free of the active ingredients of the test drug, and their color, taste and odor were similar to those of Shengyu decoction, and 1 dose was given daily in 2 doses for 14 days.

### Randomization and allocation

2.5

After qualifying for screening, patients will be randomized into 2 groups with an allocation ratio of 1:1. The randomization will be created via SAS PROC PLAN software (SAS Inc., Cary, NC) by an independent third-party clinical research organization (Institute of Basic Research in Clinical Medicine, China Academy of Chinese Medical Science) and hid from the researchers by a senior data manager who is not involved in the study. The group assignment list will be sealed in light-blocking envelopes and be opened by the researchers following informed consent procedures and baseline testing.

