### Blinding

2.8

All investigators, physicians, nurses, patients, assessors, statisticians, and participants remained blinded to group assignment until the trial ended, when all statistical analyses were finished. If any clinically significant adverse events occur after the first dose that are potentially treatment-related, the study physician will re-evaluate the participant and the PI will determine whether unblinded treatment is necessary. If non-blinding is required, the allocation information will be provided.

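### Section 2.5 has researchers open each patient's group assignment, which contradicts the blinding of all investigators in section 2.8

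*Protocol article*

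**What the plan says.** Four parts of the protocol article bear on who knows the arm.

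- **Section 2.5, Randomization and allocation.** An independent organisation generates the sequence, which is "hid from the researchers by a senior data manager who is not involved in the study". Then: "The group assignment list will be sealed in light-blocking envelopes and be opened by the researchers following informed consent procedures and baseline testing".
- **Section 2.8, Blinding.** "All investigators, physicians, nurses, patients, assessors, statisticians, and participants remained blinded to group assignment until the trial ended". On release of the code, after a potentially treatment-related adverse event: "If non-blinding is required, the allocation information will be provided".
- **Section 2.4, Intervention.** The control granules are a placebo, and "their color, taste and odor were similar to those of Shengyu decoction".
- **Section 2.2, Study design** (and the abstract, in the same terms). "This study is a prospective, outcome assessor-, and data analyst-blinded randomized controlled clinical trial".

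**The concern.** A researcher who opens an envelope holding the group assignment is no longer blind to it. Section 2.5 makes this a routine step for each patient, whereas section 2.8 treats release of the allocation as an exception that follows a safety review.

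If the opener also influences care, knowledge of the arm can reach the outcomes through differential management. Transfusion is the clearest route. Patients qualify with a day-1 hemoglobin below 8 g/dL (section 2.3), the same level that the Introduction gives as the restrictive transfusion threshold. The Introduction also says that transfusion raises hemoglobin in the short term, and hemoglobin is the primary outcome. Time out of bed and discharge to home also depend on staff decisions.

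The trial report would also claim blinding of investigators, physicians and nurses that the procedure as written does not deliver. This cannot be put right once patients have been enrolled.

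**Working it through.** The point depends on no figure in the sample size or analysis sections, so the check is a comparison of the statements.

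**1. Do sections 2.5 and 2.8 speak of the same information?** Yes. Both use the term group assignment. Section 2.5 discloses it to researchers; section 2.8 withholds it from all investigators.

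**2. Do they speak of the same people?** On the text, yes. Section 2.5 uses one word, researchers, both for those from whom the sequence is hidden and for those who later open the envelopes. Opening follows consent, and on consent section 2.6 says that "the investigator must obtain the consent of the" patient's immediate family as well as the patient's own. That places the step just before opening with a role that section 2.8 lists as blinded. No separate unblinded dispenser or pharmacist is named.

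**3. Could the envelope hold only a code?** That would remove the conflict, but the article mentions no kit numbers, coded packs or drug codes. What it puts in the envelopes is the group assignment list.

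**4. What remains protected?**
- Allocation concealment: opening comes after consent and baseline testing, so the decision to enrol that patient is made without knowing the arm.
- Patient blinding: the placebo resembles the active granules.
- Assessor and analyst blinding: intact provided these people are not the openers.

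**5. What is exposed, and under what condition?**

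| Outcome | Route | Condition |
|---|---|---|
| Hemoglobin (primary) | Co-treatment, chiefly transfusion | Opener influences care |
| Hidden blood loss | Transfusion, through the formula | Opener influences care |
| Time out of bed, discharge to home | Staff decisions | Opener influences care |
| Harris score, 2 examiner items | Rating | Opener also examines |
| Harris score, 8 patient-reported items | None direct while patients stay blind | – |

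For hidden blood loss, section 2.9.2 gives

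TBL = TRBCL / Hct(pre) + BVtrans, and HBL = TBL − VBL.

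Substituting, HBL = TRBCL / Hct(pre) + BVtrans − VBL. Reading BVtrans as the transfused volume, it enters as an added term, so a difference in transfusion between arms feeds into this outcome directly as well as through the postoperative hematocrit. The examiner items are those in "2 questions in the physician physical examination section".

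**6. How many patients?** Section 2.11 plans 36 per group: 2 × 36 = 72. If the rule in section 2.5 is followed as written, it applies to each of them.

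**The case against.** The strongest defence is that this is loose wording in a condensed article. Section 2.8 is the dedicated blinding section, is explicit, and has its own procedure for releasing the code. The look-alike placebo shows that blinding was intended. Kit coding and dispensing could well be described in the full protocol or in the operating procedure mentioned under Quality control. This lowers the certainty that staff will in fact be unblinded. It does not remove the conflict: the article makes two affirmative statements that cannot both be true, which is different from leaving a detail out.

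Several stronger readings are tempting, and the document does not support them.

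- **That the matched placebo is wasted.** It can still blind patients and supports assessor blinding. What is lost is the blinding of those who open the envelopes.
- **That the whole ward team and the full Harris score are exposed.** The article does not say that openers treat, mobilise, discharge or examine patients, and assessor blinding is stated in the abstract, section 2.2 and section 2.8.
- **That the abstract and section 2.2 add a third contradictory version.** They name assessor and analyst without saying that no one else is blinded. This is narrower than section 2.8 and should be aligned, but it is not strictly incompatible.
- **That opening a list reveals later allocations.** The article speaks of envelopes in the plural, which fits one per patient.

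**Conclusion.** The contradiction between sections 2.5 and 2.8 is real and should be settled before enrolment. Followed as written, the opening researchers know the arm of every patient they enrol, and the claim of full blinding would be untrue for them.

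This conclusion rests on taking section 2.5 at its word: the envelope shows the arm, and the openers belong to the roles listed in section 2.8. How far outcomes are affected rests on a further assumption that the article neither states nor excludes, namely that openers influence care or examine patients. Hemoglobin is a laboratory value, so bias in the primary outcome would come through differential co-treatment rather than through measurement. The size of any bias cannot be computed from the document.

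**What to change.** **Preferred.** Change section 2.5 so that active and placebo granules carry sequential kit numbers, and the envelope or dispensing log gives the researcher only the next number. The independent data manager keeps the code list, with one sealed code-break per patient for the unblinding foreseen in section 2.8. Align the blinding description in the abstract and section 2.2 with the result.

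**If researchers will in fact see the arm.** Restrict the claim in section 2.8 to patients, assessors and analysts, and state that those who open envelopes do not assess outcomes.

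**Cost.** Some relabelling, code-keeping and rewording. A placebo with similar color, taste and odor is already planned, and an independent organisation already generates the sequence, so the burden should be modest. The article does not say who packs or labels the granules, so that task has to be assigned to someone outside the blinded team.
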